### Data collection and measurements

Data will be collected through questionnaires that will be filled out by the primary caregiver of the child at baseline (time of inclusion) and after a follow-up period of twelve months. The questionnaires can be completed on paper or digital through a secured website. All questionnaires consist of valid and evidence-based instruments; details are described below. In the questionnaire, the participants can indicate whether they want support by a professional caregiver; if so, they will be referred accordingly.

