To study the exposure of parents to (elements of) parenting interventions and other types of parenting support in the daily practice of the preventive youth health care.To investigate the associations between the exposure to (elements of) parenting interventions and other types of parenting support and outcomes in parents and children related to parenting and child development (see below).

The hypothesis is that parents/caregivers who receive (elements of) parenting support during the follow-up period will show (relatively more) improvements in parenting skills, family functioning and child development compared to comparable parents/children who did not receive parenting interventions.

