### Study design

The design is a naturalistic effect evaluation [19]. It is an observational prospective cohort study with a baseline and follow-up measurement (12 months after inclusion). The total study sample will consist of parents with various levels of parenting problems and concerns. Both at baseline and at follow-up, all participating parents/caregivers will be asked to complete a questionnaire. There are no separate intervention and control groups in this study. The exposure of parents/caregivers to (elements of) parenting support during the follow-up period will be established by the follow-up questionnaire and from electronic files of the youth health care organizations (only with permission by the study participants, see below). By comparing the outcome measures between baseline and follow-up measurements, we aim to investigate which interventions and/or elements of parenting support are associated with a relative decrease in problems and improvement in positive outcome measures in parents and their children.

Data collection started in October 2017 and will continue until April 2020.

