### Participants and recruitment

We aim to include a total of net 1000 families in the cohort study. Recruitment will take place in two parts.

Part A) A sample of net 800 parents/caregivers of children aged 0–7 year will be included by two regional preventive youth health care providers (CJG Rijnmond and Rivas Zorggroep) in the regions of Rotterdam and Dordrecht, the Netherlands. These preventive youth health care organizations will inform a sample of parents/caregivers of children aged between 15 and 21 months and children aged 5 or 6 years (second grade of primary school) from their registries about the study, and invite them to participate. All invited parents/caregivers will receive project information, an informed consent form and a baseline questionnaire. Parents/caregivers who are willing to participate are requested to return the completed baseline questionnaire and the signed informed consent form to the researchers in a pre-paid envelope or via internet. All parents/caregivers who provide informed consent and a completed questionnaire are enrolled in the study.

Part B) Part B concerns an opportunity sample of net 200 parents/caregivers of children aged 0–7 year who will participate in a parenting intervention during the follow-up period. Preventive youth health care organizations and other providers of parenting support are informed about the study. They are asked to inform parents who participate in interventions about the study. The procedure regarding study information, informed consent and data collection is similar as for the parents in part A. In addition, participants are recruited directly through advertisements on websites about parenting. They will be directed to the digital version of the project information, the informed consent form and the questionnaire. All parents/caregivers who provide informed consent and a completed questionnaire are enrolled in the study.

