### Data management and statistical analysis

Data are handled according to the guidelines of the EU General Data Protection Regulation (GDPR). Data-management and analysis will be carried out at the Erasmus MC University Medical Center. Paper questionnaires will be transferred into electronic files and checked for missing or incorrect data. All data are handled confidentially and scientific data are stored anonymously.

Descriptive statistics will be used to describe the characteristics of the study population. We will use linear regression analysis for continuous outcome measures, and logistic regression analysis for dichotomous outcome variables. The exposure to (elements of) parenting interventions (yes/no) is the independent variable. In additional models, the baseline measurements and potential confounders (e.g. demographic characteristics of the caregivers and children) will be added. It will be evaluated whether additional multi-level regression analyses should be performed given the potential clustering within the youth health care organizations in the study. The exposure to parenting support will be based on information obtained from the follow-up questionnaire and when available the electronic files of the youth health care organizations. All analyses will be performed using SPSS version 24 for windows and R (version 3.4.1). Missing data will be handled by multiple imputation. All tests will be two-sided and *p*-values less than 0.05 will be considered as significant.

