## Discussion

This article describes the study protocol of a prospective cohort study that is part of the CIKEO consortium study (Consortium Integration Knowledge promotion Effectiveness Of parenting interventions). The overarching aim of the CIKEO consortium is to investigate preventive parenting interventions, in order to identify effective elements within these interventions. The aim of the prospective cohort study is to investigate the exposure of parents/caregivers to parenting support elements and strategies in daily practice of Dutch preventive youth health care and the effects of this exposure on parenting skills, family functioning and child development in a naturalistic effect evaluation. We hypothesize that parents/caregivers who have been exposed to elements of parenting support during the follow-up period will show significant improvements in specific outcome variables related to parenting skills, family functioning and child development when compared to comparable parents/children who not have been exposed to parenting interventions.

This study has several strengths. First, the data are collected in a naturalistic setting, as the cohort study is conducted in the setting of daily youth health care practice. This enables us to explore the effects of parenting interventions in the “real world” rather than in an experimental setting, which will support the generalizability of our findings [19]. Furthermore, we will not only examine the effects of parenting interventions but also the effects of other types of parenting support provided by preventive youth health care. These types of parenting support are important to take into account, as previous research has indicated that such parenting support can also have relevant effects [43].

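### Referral offered through the study questionnaire may create part of the exposure that is counted as daily practice, and the exposure rule does not separate it

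*Protocol article*

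**What the plan says.** Under Data collection and measurements, questionnaires are completed "at baseline (time of inclusion) and after a follow-up period of twelve months". The same section adds: "In the questionnaire, the participants can indicate whether they want support by a professional caregiver; if so, they will be referred accordingly". Under Participants and recruitment, for Part A, "All invited parents/caregivers will receive project information, an informed consent form and a baseline questionnaire"; the procedure for Part B is described as similar.

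Exposure is defined by what happens after baseline. Study design says: "The exposure of parents/caregivers to (elements of) parenting support during the follow-up period will be established by the follow-up questionnaire". The statistical section repeats the sources ("The exposure to parenting support will be based on information obtained from the follow-up questionnaire and when available the electronic files") and fixes the form of the variable: "The exposure to (elements of) parenting interventions (yes/no) is the independent variable". The section on parenting interventions and support also brings consultations about parenting into scope, so a referral need not lead to a full programme to count.

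The first objective is "To study the exposure of parents to (elements of) parenting interventions and other types of parenting support in the daily practice", and the Discussion gives as the first strength: "First, the data are collected in a naturalistic setting, as the cohort study is conducted in the setting of daily youth health care practice".

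**The concern.** The study offers a route to professional help at the start of the window in which it then counts help received. Support that arises this way is coded the same as support that daily practice would have supplied. The follow-up items described cover duration, frequency, character, content and appreciation of support; what prompted it is not among them. The limitations in the Discussion name hard-to-reach parents, confounding and implementation quality, but not this.

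Two things are at stake. For objective 1, the exposure frequency can overstate what daily practice delivers, and no covariate adjustment repairs a frequency. For objective 2, study-triggered exposure can arise only in families who ask for help, which strengthens the link between help-seeking and exposure. The general questions on concerns and need for support are described as additions at follow-up, after exposure. A request made at baseline would be a marker of help-seeking taken before exposure, and the article gives it no stated role.

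**Working it through.** **Inputs from the article.** Power considerations: 1000 enrolled, 40% drop-out, 600 completers, 50% (300) exposed, average cluster size 24, ICC 0.02, two-sided alpha 0.05, power 0.80, detectable difference 0.27 SD. Participants and recruitment: 800 in Part A and 200 in Part B.

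**Not given, so assumed.** The request rate, the uptake of referral, and the share of requesters who would have received support anyway. The main illustration uses a request rate of 5-15% and uptake of 100% as an outer case. A wider grid uses request rates of 2-20% and uptake of 30-80%.

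**1. The plan's own figure.** Design effect = 1 + (24 - 1) × 0.02 = 1.46. Effective size per group = 300 / 1.46 = 205.5. Detectable difference = (1.960 + 0.842) × √(2 / 205.5) = 0.276 SD. The stated 0.27 SD is this value cut to two decimals. It reproduces and is not in dispute.

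**2. Bounds on daily-practice exposure, all requesters exposed.** Requesters = 600 × rate. Upper bound = 300/600, if none of their exposure is study-induced. Lower bound = (300 - requesters)/600, if all of it is. The last column is exposure among parents who did not ask, (300 - requesters)/(600 - requesters).

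| Request rate | Requesters | Share of 300 exposed | Upper bound | Lower bound | Non-requesters only |
|---|---|---|---|---|---|
| 5% | 30 | 10% | 50% | 270/600 = 45% | 270/570 = 47.4% |
| 10% | 60 | 20% | 50% | 240/600 = 40% | 240/540 = 44.4% |
| 15% | 90 | 30% | 50% | 210/600 = 35% | 210/510 = 41.2% |

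The last column stays the same wherever the truth lies between the two bounds. At 15%, it is 41.2% whether true daily-practice exposure is 50% or 35%.

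**3. Lower uptake.** Triggered families = 600 × rate × uptake, taken as otherwise unexposed.

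- 2% and 30%: 3.6 families, 1.2% of the exposed, lower bound 49.4%.
- 5% and 50%: 15 families, 5% of the exposed, lower bound 47.5%.
- 20% and 80%: 96 families, 32% of the exposed, lower bound 34%.

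**4. Part B.** These parents are recruited because they will take part in an intervention, so a request from them should hardly change yes/no exposure. With equal drop-out, Part A has 800 × 0.6 = 480 completers. If only Part A requesters can be study-induced, 5-15% gives 24-72 families, and the pooled lower bound becomes 276/600 = 46% to 228/600 = 38%.

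**5. Precision of a sensitivity analysis without study-referred parents.** Detectable difference = 2.802 × √(1.46 × (1/n exposed + 1/300)). With 270 exposed it is 0.284 SD; with 210 exposed it is 0.305 SD. The full sample gives 0.276 SD.

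**The case against.** The strongest reply is that referring a parent who asks is close to what Dutch preventive youth health care does anyway. The article describes a free service with about 95% attendance that looks for parenting problems early and directs families to help. Many requesters might have been referred without the study. This stands, and it is why the effect is a range whose upper end is no distortion at all.

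Several stronger readings are tempting, and the article does not support them:

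- A reader might infer that every participant is asked at baseline. The sentence refers to the questionnaire without saying which one, and says participants can indicate a wish. Baseline is a fair reading because questionnaires are completed at both times. A referral from the 12-month form would fall after the exposure window and do no harm here.
- A reader might infer that nearly all requesters become exposed. Uptake is not stated. The professional in question is not defined either, and the help could be medical or psychological care, which the article lists separately from parenting support.
- A reader might infer that objective 2 suffers a bias close in size to the detectable difference. Any such figure needs an assumed gap between requesters and other exposed families, and the article gives none. With an assumed gap of 0.5 SD at baseline, the exposed-group mean shifts by 0.5 × 1.2% = 0.006 SD to 0.5 × 32% = 0.16 SD over the wide grid. That is a crude shift, before the additional models bring in baseline scores and confounders.
- A reader might infer that the request is excluded from the analysis. The confounder list is open, with demographics as an example, and the final covariate set may be fixed in a fuller document. Residual confounding is also acknowledged.

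What remains is the exposure rule as written. It counts study-triggered support as daily-practice exposure, and a choice of covariates cannot correct that.

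**Conclusion.** The point holds as a built-in possibility of unknown size. If parents ask for support at baseline and take up parenting support as a result, the stated rule can overstate daily-practice exposure, and the naturalistic claim needs qualifying. With 5-15% requesting and full uptake, 10-30% of the exposed group would be requesters, and daily-practice exposure would lie between 50% and 45-35%. Lower uptake, or requests from Part B, narrow that range. At the mild end of the assumptions the effect is negligible.

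For objective 2 the concern is weaker, because planned adjustment for baseline scores and the open confounder list cover part of it. The power statement is unaffected. It would also be wrong to take exposure among non-referred parents as the daily-practice figure: that drops help-seekers who would have received support anyway, and it equals the truth only by coincidence.

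**What to change.** Leave the referral unchanged.

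1. Keep the baseline request, and whether a referral followed, as analysis variables.
2. For objective 1, report exposure overall and again with support that followed a study referral counted as not exposed, and present the two as upper and lower bounds. Parents who also received other support still count as exposed. The bounds assume that the questionnaire affects exposure only through referral and does not displace other support.
3. For objective 2, add the baseline request as a covariate in the adjusted model, and repeat the analysis without study-referred parents.
4. State in the limitations that the measurement can itself trigger support, and qualify the naturalistic claim accordingly.

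The cost is some extra analysis and a small loss of precision in the sensitivity analysis (0.284-0.305 SD detectable instead of 0.276 SD under the 5-15% illustration). One point needs confirming first: the article's summary of the care items in the baseline questionnaire does not name the request item, so the team should check that the answers and resulting referrals are stored as usable data. If they are not, the bounds cannot be computed and only the limitation statement remains.

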### Outcome measures

The outcomes of this study are variables related to parenting, family life and child development. Unless otherwise specified, measures will be assessed at baseline as well as at follow-up.

General parenting styles and parental practices will be measured using two scales previously described by Wake [26]. The sub scale ‘warmth’ comprises six items from the Child Rearing Questionnaire [27] addressing the frequency of warm affectionate behaviors of parents towards their children. The sub scale ‘control’ includes five items from the National Longitudinal Survey of Children and Youth (Statistics Canada. National Longitudinal Survey of Children), addressing the frequency with which parents set and enforce clear expectations and limits. Items will be rated on 5-point scales, ranging from 1 (never/almost never) to 5 (all the time). The warmth and control sub scales will be used to define four parenting styles: authoritative (high warmth and high control), authoritarian (low warmth and high control), permissive (high warmth and low control), and disengaged (low warmth and low control).

Dysfunctional discipline strategies in parents will be measured with the Parenting Scale (PS) [28]. The PS consists of 30 items. Each item is rated on a seven-point Likert scale, ranging from a high probability to use an effective discipline strategy to a high probability of using ineffective discipline strategies. One item (When my child misbehaves, I spank, slap, grab, or hit my child) will not be assessed in this study, due to perceived invasiveness to parent(s)/caregiver(s). Three subscales will be computed: over-reactivity, laxness and verbosity.

Daily parenting stress will be measured with the Parenting Daily Hassles Scale (PDH) [29, 30]. The measure consists of 20 typical daily events in parenting and parent-child interactions. Parents/caregivers will be asked to rate the frequency of each potential hassle in the previous week on a 4-point scale (rarely, sometimes, a lot, constantly). Additionally, they will rate the intensity of the hassles on a 5-point scale, ranging from 0 (no burden) to 4 (great burden).

Parents’/caregivers’ satisfaction with parenting and their self-efficacy in the parenting role will be assessed with the Parenting Sense of Competence Scale (PSOC) [31]. The PSOC contains 17 items with two subscales: satisfaction and efficacy. Parents indicate their agreement with a series of statements regarding degree of confidence and satisfaction in carrying out their parenting role on a 6-point Likert scale (1 = strongly agree, 6 = strongly disagree). Higher scores indicate higher levels of parenting self-efficacy and satisfaction.

Family stress will be assessed by the seventh subscale (General Functioning) of the Family Assessment Device (FAD) [32, 33]. The FAD is a self-report measure of family functioning. The General Functioning scale consists of 12 items about support and stress within the family, providing a measure of overall health/pathology of the family. Each item receives a score from 1 (strongly agree) to 4 (strongly disagree), with the scale for the negatively worded items reversed. The sum of values is divided by 12 to give a total score ranging from 1 to 4. Higher scores indicate poorer family functioning.

Children’s emotional and behavioral problems will be assessed using the Child Behavior Check List (CBCL/1,5–5) [34]. The CBCL contains 99 items concerning the child’s behavior in the previous 2 months. Each item is scored on a three-point scale with 0 (not true), 1 (somewhat or sometimes true) and 2 (very true or often true). The CBCL includes seven empirically-based syndrome scales: emotionally reactive, anxious/depressed, somatic complaints, withdrawn, sleep problems, attention problems, and aggressive behavior. Two broad band scales can be derived. An internalizing problem score can be derived by summing the subscales emotionally reactive, anxious/depressed, somatic complains, and withdrawn and an externalizing problem score can be derived by summing the subscales attention problems and aggressive behavior scales. A total problem score can be computed by summing all 99 items. Additionally, there are five scales oriented at the Diagnostic and Statistical Manual for Mental Disorders (DSM); affective problems, anxiety problems, pervasive developmental problems, attention deficit/hyperactive problems, and oppositional defiant problems. Higher scores indicate higher levels of emotional and behavioral problems.

Other outcomes are sleep, eat and cry behaviors of the child. Parents’/caregivers’ ratings of the prevalence of problems and their concerns regarding these behaviors are assessed with 9 items for sleep behaviors, 5 items for eat behaviors and 2 items for cry behaviors.

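### The only child-behaviour form named is labelled for ages 1.5 to 5 years, yet every Part A child recruited at 5 or 6 years is 6 or 7 at the twelve-month follow-up

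*Protocol article*

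**What the plan says.** Under Outcome measures, the protocol article states that children's "emotional and behavioral problems will be assessed using the Child Behavior Check List (CBCL/1,5–5". It describes one 99-item form with seven syndrome scales, two broad-band scores, a total score and five DSM-oriented scales. No other form is named for children outside the labelled ages. The same section sets the timing: "Unless otherwise specified, measures will be assessed at baseline as well as at follow-up". No exception is made for the CBCL.

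Under Participants and recruitment, Part A is introduced as "A sample of net 800 parents/caregivers of children aged 0–7 year will be included", but the families invited are those of "children aged between 15 and 21 months and children aged 5 or 6 years". Part B is an "opportunity sample of net 200 parents/caregivers of children aged 0–7 year". Data collection and measurements places the questionnaires "at baseline (time of inclusion) and after a follow-up period of twelve months" and adds: "All questionnaires consist of valid and evidence-based instruments".

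Data management and statistical analysis specifies linear or logistic regression with exposure (yes/no) as the independent variable. Further models add the baseline measurement and potential confounders, with demographic characteristics of caregivers and children as the example. It mentions neither age strata nor a rule for CBCL scores from children outside the form's ages.

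**The concern.** The recruitment ages, the interval and the form are each stated plainly, and they do not fit together. One of the two age groups targeted in Part A has outgrown the form by the time the outcome is measured, while the article describes all its questionnaires as valid. This is a conflict between statements in the article, not a detail left to a fuller document.

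Child development is one of the three outcome domains in the hypothesis. The CBCL is the only named standardised scale among the child outcomes; the others are item ratings of sleeping, eating and crying. If CBCL scores from 6- and 7-year-olds enter the analysis on the same footing as those from toddlers, the conclusion on emotional and behavioural problems would extend to ages for which the named form is not labelled.

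**Working it through.** **Inputs.** The form's range is read from its printed label, 1.5 to 5 years. The lower limit is 18 months. The upper limit is 60 months on a strict reading, or anything under 72 months (up to the sixth birthday) on a generous one. Recruitment ages are from Participants and recruitment, and the interval of 12 months is from Data collection and measurements.

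**Ages against range.**

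| Group | Baseline | In range? | Follow-up (+12 months) | In range? |
|---|---|---|---|---|
| Part A younger | 15–21 months | Only from 18 months | 27–33 months | All |
| Part A older | 60 to <84 months | 6-year-olds out; 5-year-olds in only on the generous reading | 72 to <96 months | None, on either reading |
| Part B | 0–7 years | Under 18 months and 6–7 years out | 1–8 years | Out if under 6 months, or 5 years and over, at baseline |

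If ages in the younger group were uniform (an assumption), the share under 18 months at baseline would be 3/6 = 50%, or 3/7 = 43% if the band runs to the end of month 21.

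**Share of Part A out of range at follow-up.** This equals the older group's share of the net 800, which the article does not give. Equal groups give 50%; an assumed range of 30–70% gives 30–70%.

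**Precision after restricting the CBCL analysis to children in range at follow-up.** First, the article's own figure under Power considerations:

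- Design effect = 1 + (24 − 1) × 0.02 = 1.46; effective size = 300/1.46 = 205.5 per group.
- Detectable difference = (1.960 + 0.842) × √(2/205.5) = 0.276 SD, against 0.27 stated. This is close enough to use the same method.

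Next, the younger Part A group alone, with 40% drop-out and an even exposure split as in the article:

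- Equal groups: 400 × 0.6 = 240 completers, 120 per group; 2.802 × √(2/120) = 0.36 SD before clustering.
- Older share 30%: 560 × 0.6 = 336, 168 per group; 0.31 SD.
- Older share 70%: 240 × 0.6 = 144, 72 per group; 0.47 SD.

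Keeping 25 clusters and the intra-class correlation of 0.02, mean cluster size falls to 240/25 = 9.6. The design effect is then 1 + 8.6 × 0.02 = 1.172, and 0.36 × √1.172 = 0.39 SD. The same step gives 0.34 SD (336/25 = 13.44, design effect 1.249) and 0.49 SD (144/25 = 5.76, design effect 1.095) at the two ends. In-range Part B children would add to these numbers.

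**For comparison, requiring in-range age at both measurements.** With equal groups and uniform ages, 400 × 0.5 = 200 of the 800 in Part A qualify. That leaves 120 completers, 60 per group, and 2.802 × √(2/60) = 0.51 SD before clustering.

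**The case against.** The age arithmetic is hard to dispute. The case on the other side concerns how far it reaches, and much of it stands.

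- **Pooling is not stated.** A reader might infer that all children are analysed together on one CBCL score. The statistical section names no stratification, but it does not rule it out either, and such detail is commonly left to a fuller protocol or analysis plan.
- **The affected share can be inflated.** Counting a child as affected when either measurement is out of range gives 0.5 + 0.5 × 0.5 = 75% of Part A. That needs both equal groups and uniform ages. It also gives a baseline covariate the same weight as the outcome, although Power considerations frames the contrast at follow-up, when the younger group is entirely in range.
- **Bias is not shown.** Exposed and unexposed families complete the same form. Baseline scores and child characteristics are to be added to the models, and child age is collected. Poor age fit may mainly add noise; it biases the contrast only if age stays related to exposure after adjustment. That is possible, because Part B is recruited through intervention use and spans other ages, but the article gives nothing from which to compute it.
- **The CBCL's weight can be overstated.** It yields 7 + 2 + 1 + 5 = 15 scores, but these overlap within one form. Calling them most of the outcomes leaves out the parenting-style classification and the sleep, eat and cry outcomes.

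What the objection does not remove is the conflict itself. The article fixes one form, its age label, both time points and the recruitment ages, and it asserts validity for all questionnaires. Adjusting for age would not bring a 6- or 7-year-old inside the form's labelled range.

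**Conclusion.** The point holds in a limited form. All Part A children recruited at 5 or 6 years are outside the labelled range of the CBCL/1,5–5 at follow-up. This needs no assumption about age distribution and does not depend on how the upper limit of 5 is read. The 6-year-olds and children of 15 to under 18 months are also outside it at baseline, and part of Part B is outside at one or both times. The validity statement is therefore not met for these children.

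The affected share of Part A at follow-up is 50% with equal groups and 30–70% over an assumed range. The article does not give the split, so no firm figure is available. The documents do not support the claims that three quarters of Part A is compromised, that pooling is planned, or that the exposure contrast is biased in a known direction. The parenting and family outcomes are not touched by this point.

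**What to change.** In the analysis plan and in the article's wording:

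1. Define the main CBCL analysis as children within 1.5–5 years at follow-up, and state which reading of the upper limit applies. Keep the baseline score as a covariate, with a sensitivity analysis excluding children under 18 months at baseline.
2. Report out-of-range children separately, as exploratory raw scores.
3. Do not combine age strata without an age-stratum-by-exposure term.
4. Limit the conclusion on emotional and behavioural problems to the ages covered, and qualify the statement that all questionnaires are valid.

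The cost is lower precision for the CBCL outcomes only. With equal groups the detectable difference is about 0.36 SD before clustering and 0.39 SD with it, from Part A alone, against the stated 0.27 SD. That is still below the 0.5 SD that the article regards as meaningful, but at a 70% older share (0.49 SD with clustering) almost no margin remains before Part B is counted. Requiring in-range age at both measurements is not advised as the main analysis, because it leaves about 120 Part A completers and 0.51 SD before clustering.

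An age-appropriate form for follow-ups not yet sent is optional. It would break the same-instrument baseline adjustment for those children, who would then need to be analysed on their own standardised score. Collection runs to April 2020, and the article does not say how many follow-ups could still change.
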